### Assessment and allocation

#### Outcome measures

Measures of outcomes will be obtained at follow-up appointments at 2, 6 and 12 months after randomisation. To maximise attendance at these follow-ups, appointments will be made by phone and then a letter will be sent confirming appointment and a reminder phone call will be made 24 hrs before the appointment. Every attempt (within ethical constraints) will be made to obtain outcome data, regardless of subject's compliance with trial protocols. Follow-up measures will be scored by an investigator who is blinded to group allocation. At 2 months, information about side effects of treatment will be collected from all participants using open-ended questioning.

Following the screening consultation, personal characteristics (age, gender, ethnicity, religion, weight, height, level of education, employment status, doctor's details and contact information) and information about symptoms of low back pain will be collected (eg DASS 21 [35]; Chronic Pain Grade Questionnaire) The following treatment efficacy variables will be measured at baseline, 2, 6 and 12 months.

1. Average pain intensity over last week (0–10 scale) [36-38]

2. Patient-generated measure of disability (Patient-Specific Functional Scale) [36-38]

3. Global perceived effect (Global Perceived Effect Scale) [36-38]

4. Condition-specific measure of disability (Roland Morris Disability Questionnaire) [36-38]

5. Recurrence at 12 months

The primary outcomes are pain, GPE and PSFS at 2 months and recurrence at 12 months.

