#### Interventions

Contemporary physiotherapy practice in exercise prescription is to assess each patient and to implement the form of exercise that is most relevant to the particular clinical presentation. At present this widely accepted approach relies primarily upon the clinical expertise of the therapist. We have elected to evaluate motor control exercise delivered in this manner because this approach is regarded as contemporary best practice.

Participants in each group will receive 12 half hour treatments over an 8-week period, i.e. 2 sessions/week in the first month and 1 session/week in the second month. The treatment sessions are designed to become less frequent over time to encourage independence and continuation of exercise when therapy is complete. This is consistent with current clinical practice.

The *motor control exercise *program is based on the treatment approach reported by O'Sullivan et al [12], Richardson et al [28], and Moseley [39]. A brief description is provided below.

At the first session, participants will be comprehensively assessed and then will be prescribed exercises aimed at improving function of specific muscles of the low back region to be conducted in sessions 2–11. Stage 1 involves the most commonly prescribed exercise aimed at retraining multifidus (a back muscle) and transversus abdominus (a deep abdominal muscle); these exercises will be supplemented with exercises for the pelvic floor muscles, breathing control and control of spinal posture. Participants will be taught how to contract these muscles independently from the superficial trunk muscles [28,40]. Physiotherapists will use real-time ultrasound biofeedback to enhance learning of the tasks. When participants are able to perform these exercises, they will be gradually upgraded until the patient is able to maintain isolated contractions of these muscles for 10 seconds, up to a maximum of 10 repetitions, during normal respiration [28]. When this level of competence has been achieved, patients will be considered ready to progress to Stage 2.

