Stage 2 of the approach involves increasing the complexity of the exercise by progressing through a range of functional tasks and exercises targeting coordination of trunk and limb movement and maintenance of trunk stability. The range and progression of exercises is well set-out in clinical texts [28] and is individualised to the patient based on this presentation. Participants require the ongoing support of a trained physiotherapist to ensure correct performance of the exercises. Session 12 is a discharge session where the patient's progress will be reviewed and patients will be prescribed exercises to continue at home.

The *placebo *intervention is 20 minutes of detuned short wave diathermy and 5 minutes of detuned ultrasound for 12 sessions over an eight week period. This attention control will be used because there is no known treatment effect from the detuned machines, but it has been established in previous trials (including one of our own [37]) that participants view this as a credible treatment. To increase the perceived credibility of the attention control, participants will undergo an examination including routine screening for contraindications at the first consultation and the normal clinical reassessment that would occur with the active forms of these interventions at each subsequent treatment. Each placebo treatment session will be 30 minutes in duration to match the active treatment sessions.

Participants in both treatment groups will be asked not to seek other treatments for their chronic low back pain and where possible not to change current medications during the treatment period. Several mechanisms will be used to ensure that the trial protocol is consistently applied. Protocol manuals will be developed and staff will be trained to ensure that screening, assessment, randomisation and treatment procedures are conducted according to protocol. To ensure standardisation across sites we will hold regular meetings with site visits and teleconferencing. An independent researcher will monitor a randomly chosen subset to ensure adherence to assessment, randomisation and treatment procedures.

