If a participant is concerned about his or her condition during the study, the physiotherapist will screen for potentially serious pathology and, where appropriate, refer the patient to a medical practitioner. The medical practitioner will be asked not to request the participant's group allocation unless it is deemed necessary for medical care. At the completion of the exercise program, patients will be encouraged to continue the home exercise routine demonstrated at the discharge session. Participants will be free to seek other treatment after the experimental period.

After the first treatment session the patient will complete a treatment credibility scale [41]. At the 8 week follow-up information about side-effects of treatment will be collected using open-ended questioning. At the 12 month follow-up the participants will be asked to rate the helpfulness, understanding and friendliness of therapist and helpfulness of treatment and to nominate which treatment they thought they received. Additionally information about other treatment received for their low back pain during the study period will be sought using open-ended questioning.

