### Justification of study design

#### Placebo

Designing an appropriate placebo treatment that mimics a physiotherapy exercise program is challenging. The sham interventions used in previous exercise trials do not satisfy the criteria of being both inert (e.g. the use of hot packs) and credible (e.g. allocation to a treatment waiting list). Accordingly, we will use sham electrotherapy as a control. This sham is clearly inert and is regarded as a credible treatment by participants. [37] To ensure that participants remain unaware of study group, it is necessary to carefully describe the study to patients. In the previous trial where we used sham electrotherapy as a control for exercise, we used the following description:

'In this trial normal physiotherapy treatment and placebo physiotherapy treatment will be provided. A placebo treatment is a harmless treatment delivered at less than the effective dose. We will not tell you which type of treatment you will receive and it is unlikely that you could distinguish them.'

Trial staff described the placebo intervention as 'pulsed ultrasound' and 'pulsed shortwave' and explained to patients that they would probably not feel any sensation during treatment.

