#### Controlling bias

The trial has been designed to include key methodological features that have been recognised as minimising bias in clinical trials. These features include: true randomisation, concealed allocation, specification of eligibility criteria, blind outcome assessment, patient blinding, blind analysis and intention-to-treat analysis. The nature of the treatments precludes blinding of treatment provider. Trial staff will be trained to ensure consistency of screening, assessment, randomisation and treatment procedures. Participant's perception of the credibility of treatment will be determined after the first treatment [41]; and at the completion of treatment both assessors and participants will be asked to identify what treatment they think the participant received.

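### Harms are collected only as side effects of treatment, so arm-dependent attribution could bias any comparison of recorded harms in either direction

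*Protocol article*

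**What the plan says.** The Protocol article describes harm collection in two places. Under Outcome measures: "At 2 months, information about side effects of treatment will be collected from all participants using open-ended questioning". Under Interventions: "At the 8 week follow-up information about side-effects of treatment will be collected using open-ended questioning". I read these as the same enquiry at the same visit. Both define what is collected by its relation to treatment, and neither mentions asking about events whatever their cause.

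The two arms differ plainly in what participants do. The exercise arm has supervised sessions that progress from isolated muscle contractions to functional tasks, with ultrasound feedback ("Physiotherapists will use real-time ultrasound biofeedback to enhance learning of the tasks") and home exercises at discharge. The placebo arm receives "20 minutes of detuned short wave diathermy and 5 minutes of detuned ultrasound for 12 sessions over an eight week period".

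The Data analysis section covers the efficacy outcomes, recurrence and one predictor of response. It states no between-arm comparison of harms.

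**The concern.** A side effect of treatment is an event plus a judgement about its cause. If collection is limited to that category, the judgement comes before the record, and an event that nobody links to treatment leaves no trace.

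That would matter little if the judgement were made alike in both arms, but the cues differ. Everyone enrolled has chronic low back pain, so flares are plausible in either group. A flare after a progressed exercise session has an obvious candidate cause, whereas one after lying under a machine has less of one. That pushes recorded harms up in the exercise arm. The opposite is also plausible: participants may regard soreness after exercise as normal and not mention it, which pushes recorded harms down.

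This is the only harm measure stated. A reader who sets the two arms side by side, with or without a test, would see true risk mixed with perceived cause. Later analysis could not recover transient or non-back events that were never recorded.

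**Working it through.** **Figures in the plan.** The documents give no event rate, attribution rate or sample size for harms. The only usable figures are 77 per group and 15% loss to follow-up (Sample size calculations). The 77 was set for efficacy, and it reproduces: 62.8 per group for a 0.50 SD difference (alpha 0.05 two-sided, power 0.80), × (1 − 0.5²) = 47.1, ÷ 0.85² for non-compliance and ÷ 0.85 for loss = 76.7, rounded up to 77. It has no bearing on harms except through the number analysed: 77 × 0.85 = 65.45, taken as 65 per arm.

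**Assumptions (not in the documents).** True event risks and attribution probabilities are chosen for illustration. The test is a two-sided two-proportion z-test at 0.05.

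**Formula.** Recorded risk in an arm = true risk × probability that an event is attributed to treatment.

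**Equal true risk of 20% in both arms, exercise versus placebo:**

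| Attribution | Recorded risk | Difference | Ratio |
|---|---|---|---|
| 50% v 50% | 10% v 10% | 0 points | 1.0 |
| 60% v 40% | 0.20 × 0.60 = 12% v 0.20 × 0.40 = 8% | 4 points | 1.5 |
| 75% v 25% | 0.20 × 0.75 = 15% v 0.20 × 0.25 = 5% | 10 points | 3.0 |

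**Chance of nominal significance.** This is Φ[(d − 1.96 × SE0)/SE1], where d is the difference in recorded risk, SE0 the pooled and SE1 the unpooled standard error. The mean recorded risk is 10% in both unequal rows, so SE0 = √(2 × 0.10 × 0.90/65) = 0.0526 and 1.96 × SE0 = 0.1031.

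- 12% v 8%: SE1 = √[(0.12 × 0.88 + 0.08 × 0.92)/65] = 0.0525. (0.04 − 0.1031)/0.0525 = −1.20, giving 0.115. Adding 0.003 for the opposite tail gives about 12%.
- 15% v 5%: SE1 = √[(0.15 × 0.85 + 0.05 × 0.95)/65] = 0.0519. (0.10 − 0.1031)/0.0519 = −0.06, giving about 48%.
- Equal attribution: about 5%, the nominal level.

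**Opposite direction.** Suppose the true risk is 30% with exercise and 15% with placebo, and attribution is 25% and 50%. The record shows 0.30 × 0.25 = 7.5% and 0.15 × 0.50 = 7.5%, so a real 15-point excess disappears. Recorded without the attribution filter, 30% v 15% would reach nominal significance with probability of about 54%.

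**What other measures would catch.** Pain, the Patient-Specific Functional Scale and the Roland Morris questionnaire are taken in both arms at 2, 6 and 12 months and need no attribution to treatment. Worsening that lasts to a visit is therefore seen. The pain item covers only the preceding week, so a flare that has settled by 2 months would not show there. The two disability measures are not designed to capture events outside the back.

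**The case against.** The strongest reply is that the article gives a topic and a method, not the question itself. An assessor could ask openly about any problem and judge its relation to treatment afterwards. The exact script may sit in the full protocol or in the protocol manuals the article promises. That stands as far as it goes: participant attribution is the natural reading, not a stated fact. But whoever makes the link, the construct named in both places admits only events linked to treatment, so this is a choice the article fixes and not a detail it leaves out.

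A second reply is that participants and the follow-up investigator are blinded and everyone is asked at the same time by open-ended questioning. These are real strengths. Yet blinded scoring acts after a symptom has been mentioned or not, and participant blinding hides which treatment is the placebo, not whether one is exercising.

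A reader might go further and infer that the two arms are given different expectations, because the Placebo section says staff "explained to patients that they would probably not feel any sensation during treatment" and contains the sentence "A placebo treatment is a harmless treatment delivered at less than the effective dose". The documents do not support this for the present trial. Both passages report what was done in the previous trial; reuse is at most implied. The second comes from a description of the study that did not tell participants their arm: "We will not tell you which type of treatment you will receive and it is unlikely that you could distinguish them". The point rests on the difference in treatment content alone.

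It would also be too strong to say that a planned harm comparison is invalid, or that the data would show blame instead of events. No such comparison is stated, and the efficacy scales capture persistent back worsening whatever its cause. What remains exposed is narrower: transient flares and non-back events.

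**Conclusion.** The point holds in limited form. The only stated harm collection filters events by their link to treatment. The arms differ enough in content for that filter to act unequally, so any later comparison of recorded harms could be biased either way. The mechanism and its two possible directions are established; the size is not. The illustrative results (a spurious 4 to 10 points with a 12% to 48% chance of nominal significance, or a true 15-point excess hidden) rest entirely on assumed event and attribution rates with 65 per arm. With equal attribution the between-arm bias disappears, although harms would still be under-counted in both arms. No stated hypothesis, primary outcome or planned test is affected. It is nonetheless worth correcting, because transient and non-back events lost at collection cannot be recovered and the correction is cheap.

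**What to change.** In both Outcome measures and Interventions, state that at the 2-month visit all participants are asked the same open-ended, cause-neutral question, for example: *Since you joined the study, have you had any new health problem, or has your back pain or any other symptom become worse?* Report all such events by arm, and record perceived relation to treatment as a separate second item, asked afterwards.

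The visit and the open-ended format stay as they are. The cost is that more unrelated complaints will be recorded and will need coding.

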#### Randomisation

Participants will be allocated to treatment group using sealed opaque envelopes. The allocation sequence will be generated by author CM. Participants will be scheduled to receive their first treatment within one week of randomisation.

#### Interventions

Contemporary physiotherapy practice in exercise prescription is to assess each patient and to implement the form of exercise that is most relevant to the particular clinical presentation. At present this widely accepted approach relies primarily upon the clinical expertise of the therapist. We have elected to evaluate motor control exercise delivered in this manner because this approach is regarded as contemporary best practice.

Participants in each group will receive 12 half hour treatments over an 8-week period, i.e. 2 sessions/week in the first month and 1 session/week in the second month. The treatment sessions are designed to become less frequent over time to encourage independence and continuation of exercise when therapy is complete. This is consistent with current clinical practice.

The *motor control exercise *program is based on the treatment approach reported by O'Sullivan et al [12], Richardson et al [28], and Moseley [39]. A brief description is provided below.

At the first session, participants will be comprehensively assessed and then will be prescribed exercises aimed at improving function of specific muscles of the low back region to be conducted in sessions 2–11. Stage 1 involves the most commonly prescribed exercise aimed at retraining multifidus (a back muscle) and transversus abdominus (a deep abdominal muscle); these exercises will be supplemented with exercises for the pelvic floor muscles, breathing control and control of spinal posture. Participants will be taught how to contract these muscles independently from the superficial trunk muscles [28,40]. Physiotherapists will use real-time ultrasound biofeedback to enhance learning of the tasks. When participants are able to perform these exercises, they will be gradually upgraded until the patient is able to maintain isolated contractions of these muscles for 10 seconds, up to a maximum of 10 repetitions, during normal respiration [28]. When this level of competence has been achieved, patients will be considered ready to progress to Stage 2.

Stage 2 of the approach involves increasing the complexity of the exercise by progressing through a range of functional tasks and exercises targeting coordination of trunk and limb movement and maintenance of trunk stability. The range and progression of exercises is well set-out in clinical texts [28] and is individualised to the patient based on this presentation. Participants require the ongoing support of a trained physiotherapist to ensure correct performance of the exercises. Session 12 is a discharge session where the patient's progress will be reviewed and patients will be prescribed exercises to continue at home.

The *placebo *intervention is 20 minutes of detuned short wave diathermy and 5 minutes of detuned ultrasound for 12 sessions over an eight week period. This attention control will be used because there is no known treatment effect from the detuned machines, but it has been established in previous trials (including one of our own [37]) that participants view this as a credible treatment. To increase the perceived credibility of the attention control, participants will undergo an examination including routine screening for contraindications at the first consultation and the normal clinical reassessment that would occur with the active forms of these interventions at each subsequent treatment. Each placebo treatment session will be 30 minutes in duration to match the active treatment sessions.

Participants in both treatment groups will be asked not to seek other treatments for their chronic low back pain and where possible not to change current medications during the treatment period. Several mechanisms will be used to ensure that the trial protocol is consistently applied. Protocol manuals will be developed and staff will be trained to ensure that screening, assessment, randomisation and treatment procedures are conducted according to protocol. To ensure standardisation across sites we will hold regular meetings with site visits and teleconferencing. An independent researcher will monitor a randomly chosen subset to ensure adherence to assessment, randomisation and treatment procedures.

If a participant is concerned about his or her condition during the study, the physiotherapist will screen for potentially serious pathology and, where appropriate, refer the patient to a medical practitioner. The medical practitioner will be asked not to request the participant's group allocation unless it is deemed necessary for medical care. At the completion of the exercise program, patients will be encouraged to continue the home exercise routine demonstrated at the discharge session. Participants will be free to seek other treatment after the experimental period.

After the first treatment session the patient will complete a treatment credibility scale [41]. At the 8 week follow-up information about side-effects of treatment will be collected using open-ended questioning. At the 12 month follow-up the participants will be asked to rate the helpfulness, understanding and friendliness of therapist and helpfulness of treatment and to nominate which treatment they thought they received. Additionally information about other treatment received for their low back pain during the study period will be sought using open-ended questioning.

#### Data integrity

The integrity of trial data will be monitored by regularly scrutinising data sheets for omissions and errors. Data will be double entered and the source of any inconsistencies will be explored and resolved.

### Data analysis

#### Treatment efficacy

In our primary analysis, we will use a regression model to test for the effect of treatment on outcome at 2, 6 and 12 months follow-up with the baseline value of the outcome entered as a covariate. A treatment effect size will be calculated for each of the follow-up time points and, if there is a statistically significant treatment effect at any time point, we will also calculate number needed to treat (NNT) to achieve pain recovery (pain < 1 out of 10: [42]) and 95% CI. The recurrence outcome will be analysed with logistic regression.

